### Missing data

Missing information for ethnicity, occupation, and other predictor variables will be reported and missing data patterns investigated. To improve completeness, we will use information from multiple data sources. Those with completely missing ethnicity information will be excluded from the main analysis. Comorbidity information will be identified using primary care records; thus, absence of comorbidity codes will be interpreted as absence of comorbidity (ie, not missing).

We will report the coverage of each analysis and the number (%) of HCWs included. Sensitivity to the exclusion of missing data will be assessed using multiple imputation methods.

### Baseline characteristics

The frequency (%) of HCWs by ethnicity and occupational group will be reported. Core predictors (age, sex, comorbidity and deprivation) will be summarised by ethnicity and occupational group using frequency (%) for categorical measures and mean (SD) or median (IQR) for continuous. We will compare core predictors between those with recorded and missing ethnicity information.

For the HR substudy, additional ethnicity, occupation and exposure predictors will be summarised alongside the core predictors where available. Changes in roles, exposure and absences over time will be described across ethnicity category and occupational group.

All baseline data will be presented for the whole cohort and by country.

A flowchart, using the STROBE format, will present cohort selection for both the broad and HR substudy analyses, with exclusions explained. Average and overall follow-up time will be summarised for each cohort, by ethnicity, occupational group, and country.

### Outcome incidence

Adjusted annual and quarterly incidence rates, per 100 000 HCWs, for each outcome will be calculated for each country where available. Meta-analysis methods will combine the country-specific estimates to give an overall UK incidence rate estimate. Adjusted incidence rates by ethnicity and occupation will be calculated in the same way. All incidence rates will be adjusted for the four core predictors (age, sex, comorbidities and deprivation) using standardisation methods. The incidence rates of each outcome will be reported as the rate of cases in the final UK HCW cohort and within subgroups who have experienced preceding COVID-19 events (table 3: COVID-19 outcomes and definitions, identified via listed data sources, to be assessed in UK HCW cohort and within listed subgroups, via listed analysis approach in the planned study). The time between diagnosis and outcomes will be summarised and cumulative incidence curves will be plotted.

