## Introduction

COVID-19 has been declared a global pandemic. Since the first reported cases in December 2019, over 110.7 million cases and 2.4 million deaths have been reported worldwide.^1^ Consistent evidence identifies advanced age, male sex, socioeconomic deprivation and chronic comorbidities as core predictors for COVID-19 adverse outcomes.^2–5^

The COVID-19 pandemic has disproportionately impacted historically disadvantaged populations.^6^ In the UK, higher infection and mortality rates are observed in areas with greater deprivation^7^ and among ethnic minorities.^8–12^ This has prompted calls to prioritise the publication of data disaggregated by ethnicity and to conduct research which increases our understanding of risk in these populations.^13 14^ Ethnicity is a complex construct which represents social, biological or genetic differences between populations.^15^ Potential explanations for COVID-19-related health disparities between ethnic groups include socioeconomic, cultural, behavioural, biological or pathophysiological differences.^16^ It is recommended that investigations into ethnicity-related health inequality should also consider interrelated factors such as deprivation, religion and pre-existing conditions. This approach serves to highlight the interplay between ethnic disparities and economic inequality^13^ and disentangle the independent importance of these factors.^14^

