### Objectives

Our primary aim is to determine whether COVID-19 diagnosis, hospitalisation and mortality rates differ between ethnic and occupational groups in HCWs. We will conduct both a broad analysis, encompassing all those registered as HCWs on 1 February 2020 in the UK, and a detailed substudy analysis in those actively working during the COVID-19 pandemic, incorporating more granular ethnicity, occupation and exposure information.

Considering current evidence, we hypothesise that HCWs from ethnic minority backgrounds will have increased risk of COVID-19 diagnosis and adverse outcomes compared with their White counterparts regardless of occupation.

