### Associations between ethnicity, occupation and COVID-19 outcomes

The relationship between ethnicity and COVID-19 outcomes will be assessed using Poisson, logistic and flexible parametric time-to-event regression models (table 3: COVID-19 outcomes and definitions, identified via listed data sources, to be asessed in UK HCW cohort and within listed subgroups, via listed analysis approach in the planned study). For each outcome, multivariable models will incorporate ethnic category and occupational group, and their interactions, adjusted for the four core predictors. The analyses will be conducted by country, and country-specific results combined using meta-analysis methods to produce UK estimates. We will report incidence rate ratios, ORs or HRs with 95% CIs and p-values. Forest plots and cumulative incidence curves will be produced. Interactions between ethnicity and other predictors will be presented graphically to aid interpretation. Model assumptions will be assessed.

We will use directed acyclic graphs to map hypothesised causal associations between ethnicity, occupational group, the core predictors and COVID-19 outcomes. Mediation analysis methods will then be applied to disentangle the direct, indirect and mediated interactive effects of ethnic category and COVID-19 outcomes. The direct effects estimated using the approach are likely to be related to unmeasured explanatory factors, including experiences of structural discrimination and racism, rather than any genetic predispositions for differing outcomes.

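### The plan specifies only ethnic contrasts adjusted for deprivation and comorbidity (and, in the models, occupation), and does not say whether the primary aim concerns a total or a conditional difference

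*Protocol article*

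**What the plan says.** All references are to the Protocol article.

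- **Objectives.** The primary aim is to "determine whether COVID-19 diagnosis, hospitalisation and mortality rates differ between ethnic and occupational groups in HCWs". No adjustment set is named. The hypothesis is that ethnic minority staff have higher risk "compared with their White counterparts regardless of occupation".
- **Introduction.** "Potential explanations for COVID-19-related health disparities between ethnic groups include socioeconomic, cultural, behavioural, biological or pathophysiological differences". The same section recommends looking at deprivation, religion and pre-existing conditions together with ethnicity, so that their separate contributions can be seen.
- **Outcome incidence.** "All incidence rates will be adjusted for the four core predictors", which are age, sex, comorbidity and deprivation, by standardisation. For the breakdown by group: "Adjusted incidence rates by ethnicity and occupation will be calculated in the same way".
- **Associations between ethnicity, occupation and COVID-19 outcomes.** "For each outcome, multivariable models will incorporate ethnic category and occupational group, and their interactions, adjusted for the four core predictors". Causal diagrams covering ethnicity, occupation and the core predictors are to be drawn, followed by a mediation analysis into direct, indirect and interactive components. The Abstract says mediation methods will be explored, and names occupational group alongside ethnicity and outcome.
- **HR sub-study** (analysis section). The models keep this covariate set and add to it.
- **Sensitivity and additional analyses.** The only listed change to the adjustment covariates is the addition of BMI and smoking.

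**The concern.** A question about whether rates differ between ethnic groups can be read in two ways. One is the overall difference between people of the same age and sex. The other is the difference that remains once they are also alike in deprivation, health and job. These are different estimands, and the plan does not say which one the aim concerns.

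If minority staff are more often deprived, in poorer health or in more exposed jobs, and these raise risk, a disparity acting through them is removed by the adjustment. A reader of the fully adjusted table could take a small ratio to mean that there is little disparity, when it means only that little is left unexplained. This matters because the study is meant to inform guidance on health inequalities, and because the disparity that motivates it in the Introduction is unadjusted: ethnic minorities are 65%–76% of reported deaths in clinical staff but less than 20% of the workforce. No specified rate or model gives a figure comparable with that one or with an age-sex-adjusted version of it.

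**Working it through.** **1. Covariates of each specified ethnic contrast.**

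| Output | Age, sex | Deprivation, comorbidity | Occupation | Further |
|---|---|---|---|---|
| Standardised rates by ethnicity | yes | yes | no | – |
| Main outcome models | yes | yes | yes, with ethnicity interaction | – |
| HR sub-study models | yes | yes | yes | ethnicity-related, occupational, exposure predictors |
| BMI/smoking sensitivity | yes | yes | yes | BMI, smoking |

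No row stops at age and sex. The text says this applies to all rates and to each outcome, so it is a stated choice and not a detail left out.

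**2. The plan's own figures.** The documents give no figure for the effect of adjustment. The nearest is the precision statement under Sample size. A simple unadjusted half-width is 1.96 × √[p(1−p)(1/n₁ + 1/n₂)].

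- Infection, p = 0.062, White n = 1.4 million × 0.792 = 1 108 800. Asian n = 140 000 gives 0.13% (stated 0.1%). Black n = 85 400 gives 0.17% (stated 0.2%).
- Mortality in the 32 042 expected diagnosed cases, p = 0.064. Asian gives 0.90% (stated 0.9%). Black gives 1.13% (stated 0.8%), which does not reproduce; the group-specific rates used are not given.

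Three of the four figures agree with an unadjusted difference. This suggests, without proving, that precision was planned for a contrast that the analysis sections do not specify. The point does not depend on it.

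**3. Illustration of what the adjustment can do.** All inputs are assumed; none comes from the documents. Deprivation, occupation and comorbidity are each treated as two-level, independent of one another, and multiplicative on the rate. For a factor with rate ratio R and prevalence p₁ (minority) or p₀ (White), its contribution is (1 + p₁(R−1)) / (1 + p₀(R−1)).

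| Scenario | Deprivation p₁, p₀, R | Occupation p₁, p₀, R | Comorbidity p₁, p₀, R |
|---|---|---|---|
| Small | 0.30, 0.20, 1.2 | 0.55, 0.50, 1.2 | 0.22, 0.20, 1.5 |
| Moderate | 0.40, 0.20, 1.5 | 0.60, 0.45, 1.5 | 0.25, 0.20, 2.0 |
| Large | 0.50, 0.20, 2.0 | 0.70, 0.40, 2.0 | 0.30, 0.20, 2.5 |

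Moderate case in full: deprivation 1.20/1.10 = 1.091; occupation 1.30/1.225 = 1.061; comorbidity 1.25/1.20 = 1.042. The product is 1.206. With a direct ratio of 1.20, the age-sex-adjusted ratio is 1.20 × 1.206 = 1.45. The four-predictor standardised ratio leaves only occupation free: 1.20 × 1.061 = 1.27. The model with occupation gives 1.20.

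| Scenario | Age-sex ratio | Planned standardised rates | Planned model | Log ratio removed by model |
|---|---|---|---|---|
| Small | 1.25 | 1.21 | 1.20 | 17% |
| Moderate | 1.45 | 1.27 | 1.20 | 51% |
| Large | 2.03 | 1.46 | 1.20 | 74% |

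The last column is 1 − ln(1.20)/ln(age-sex ratio), using unrounded ratios. With a direct ratio of 1.00, the age-sex ratio is 1.04, 1.21 or 1.69, while the model shows 1.00.

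**The case against.** **The aim does not ask for an age-sex-adjusted difference.** A reader might infer that the plan fails to answer its own primary question. The documents do not support that. The Objectives name no adjustment set, the hypothesis is framed irrespective of occupation, and the Introduction argues for separating deprivation and pre-existing conditions from ethnicity. These are good reasons to keep the conditional analyses. They do not explain why those should be the only ones specified.

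**The mediation analysis could supply a total.** A reader might also infer that no total difference can ever come out of this plan. That goes too far: the direct, indirect and interactive components can be summed. What remains is that the plan names no total effect, describes the method in the Abstract as something to be explored, and names only occupational group as the intermediate there. A total built that way may still be conditional on deprivation and comorbidity.

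**Causal order is left to the diagrams.** The article calls deprivation and comorbidity core predictors, and occupation is an exposure of primary interest in its own right. That they follow from ethnicity is therefore an assumption, and the point has to be put conditionally.

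**There is some protection against misreading.** The plan attributes direct effects to unmeasured factors such as structural discrimination, and it tabulates the core predictors by ethnicity. This helps the reader, but it gives no overall contrast.

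**Is this only reporting detail for the full analysis plan?** It would be if the article were silent. It states its adjustment set explicitly and universally.

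**Conclusion.** The point holds in this form: the aim leaves open whether a total or a conditional ethnic difference is wanted, and the plan specifies only conditional ones. To the extent that deprivation, comorbidity and occupation lie on the path from ethnicity to outcome, the specified contrasts are nearer to direct than to total differences.

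The size cannot be derived from the documents. In the illustration the planned model removes between 17% and 74% of the log ratio, and that width reflects the assumed inputs. Understatement requires minority staff to carry more of the factors that raise risk; if some factor ran the other way, its adjustment would raise the ratio. The illustration also assumes independent factors on a rate-ratio scale and no ethnicity-by-occupation interaction.

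The planned conditional analyses are not wrong and should stay. This is a worthwhile and inexpensive improvement to the plan.

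**What to change.** 1. State in the Objectives whether the ethnic difference of primary interest is total, conditional or both.
2. For each outcome, report standardised rates and models by ethnicity in steps: age and sex only; then deprivation and comorbidity added; then occupation added, ending with the planned model and its interaction.
3. In the mediation analysis, commit to stating the total effect with its components, and say what it is conditional on.
4. Label the fully adjusted estimate as the difference not explained by deprivation, comorbidity and occupation.

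**Cost.** Extra model runs per outcome and extra table columns, from variables already being collected. Nothing planned is dropped. Several estimates per outcome need care in interpretation. In particular, odds ratios and hazard ratios can change between steps for reasons other than mediation (non-collapsibility), so comparisons across steps are best read from the standardised rates.

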### Study population

The cohort will include all adult (aged 16 years and over) HCWs captured by HR records or registered with at least one professional regulator on 1 February 2020, excluding those which linkage to EHRs is unsuccessful. HCWs with missing ethnicity, occupation, age, sex or postcode will be excluded from the main analysis. For the HR substudy, only those actively working will be included, thus excluding those on parental, sickness or disability leave for the duration of study period.

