### Main exposures

The main exposure of interest is ethnicity, which is likely to be inconsistently recorded across databases. We will primarily assign ethnicity using staff HR records (ESR or SWISS) and registration databases (if not included/missing from HR records). If ethnicity is missing from these databases, linked EHRs will be assessed. Those with ethnicity recorded as ‘not stated’ or with completely missing ethnicity information will be excluded from the main analyses. Ethnicity will be categorised based on ONS groupings (table 2).

**Table 2 T2:** ONS ethnicity groupings

Broad ethnic categories	Ethnic groups
White	English/Welsh/Scottish/Northern Irish/British Irish Gypsy or Irish Traveller Any other White background
Mixed/multiple ethnic groups	White and Black Caribbean White and Black African White and Asian Any other mixed/multiple ethnic background
Asian/Asian British	Indian Pakistani Bangladeshi Chinese Any other Asian background
Black/African/Caribbean/Black British	African Caribbean Any other Black/African/Caribbean background
Other ethnic group	Arab Any other ethnic group

ONS, Office for National Statistics.

A more granular analysis will incorporate subdivisions of ethnicity (particularly within Asian/Asian British category) if a sufficient number of events are observed.

Occupational group (and its interaction with ethnicity) is also of primary interest. We will assign occupation for the main cohort using data recorded on 1 February 2020 from either HR records or data held by the regulating bodies and the following categories informed by version 17.1 of the NHS Occupational Code Manual (*NHS Digital*):

Ambulance staffAdministrations and estates staffHealthcare assistants and other support staffMedical staffDental staffNursing, midwifery and health visiting staffNursing, midwifery and health visiting learnersScientific, therapeutic and technical staffHealthcare sciencesGeneral payments

A more granular analysis will incorporate subdivisions of occupational groups (particularly the Medical staff group) if a sufficient number of events are observed.

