The broad analysis will examine associations between ethnicity, occupational group and multiple important COVID-19 outcomes in HCWs employed in the UK, while adjusting for core predictors. Using readily available EHR data enables the investigation of complex models of public health resulting in scalable, population-based measurements of disease burden.^33^ However, we foresee a trade-off between the scale and depth of the data, for example, while incorporating professional registration databases captures HCWs in non-NHS sectors, we are unable to identify whether they are actively working (not retired, on parental or long-term sick leave). Thus, a substudy will use detailed NHS HR databases to enable granular analyses of ethnicity, occupation and COVID-19 exposures in those actively working during the pandemic. Additional hypothesis generating analyses will be conducted where interesting results are found, for example if the study identified a higher mortality incidence in a particular ethnic group, a more detailed analysis investigating differences in disease severity by ethnic group could be planned.

Implications regarding the quality of the EHR data have been considered; multiple data sources will be utilised to limit the impact of missing information for the main exposures (ethnicity and occupation) and outcomes (diagnosis, hospitalisation, death). However, ethnicity information is notorious for being poorly recorded in EHR data and the missing information is unlikely to be missing at random. Even after taking steps to limit the impact of missing information, utilising a complete-case analysis approach may still introduce some sampling bias. Sensitivity analyses are planned to account for predictors expected to have high proportions of non-random missingness, such as ethnicity, BMI and smoking status. However, this study will be limited by the subset of COVID-19 cases that are diagnosed and recorded within the EHR data. Many HCWs with SARS-CoV-2 infections will not be diagnosed, with a US study projecting up to 63%.^28^ Indeed, the study will not capture HCWs with mild or asymptomatic infections in settings where tests are restricted to those with symptoms, and results may be vulnerable to collider bias.^31^ Incorporating both suspected and confirmed COVID-19 diagnoses is likely to increase the number of infections captured, though it is also likely to reduce the specificity of diagnosis by incorporating false positive cases.

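### On the natural reading, staff with unknown ethnicity are dropped from overall, country and occupation-specific incidence rates that do not use ethnicity; these rates should keep them

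*Protocol article*

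**What the plan says.** All references are to the protocol article.

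- **Study population** defines the cohort as adult healthcare workers in HR or regulator records on 1 February 2020, less those whose linkage fails. A separate sentence then says "HCWs with missing ethnicity, occupation, age, sex or postcode will be excluded from the main analysis".
- **Main exposures** takes ethnicity from HR records, then from registers, then from linked health records. Staff whose ethnicity is not stated "or with completely missing ethnicity information will be excluded from the main analyses". No cut-off date is given for the health-record lookup.
- **Sample size** says the sample will be driven by the number of staff who have complete exposure data and are successfully linked.
- **Outcome incidence** plans rates by country, for the UK, by ethnicity and by occupation. On adjustment: "All incidence rates will be adjusted for the four core predictors (age, sex, comorbidities and deprivation) using standardisation methods". On the population: "The incidence rates of each outcome will be reported as the rate of cases in the final UK HCW cohort", and also subgroups with a preceding COVID-19 event.
- **Baseline characteristics** plans one named contrast of the two groups: "We will compare core predictors between those with recorded and missing ethnicity information".
- **Missing data** adds "Missing information for ethnicity, occupation, and other predictor variables will be reported and missing data patterns investigated" and "Sensitivity to the exclusion of missing data will be assessed using multiple imputation methods". **Sensitivity and additional analyses** repeats the imputation and lists a missing-ethnicity analysis, both subject to the numbers captured.
- **Discussion and limitations** says ethnicity is unlikely to be missing at random and that "utilising a complete-case analysis approach may still introduce some sampling bias".

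**The concern.** A rate needs only the variables that define and standardise it. The overall and country rates need the four core predictors, and the occupation rates need occupation as well. Removing people from numerator and denominator because a further, unused variable is unknown brings no analytic gain. It biases the rate whenever the removed staff have a different outcome rate given the core predictors, and standardising on those predictors cannot repair that.

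The ethnicity rule offers a plausible route to such a difference. A person whose ethnicity is absent from HR and register data is kept only if a health record supplies it. Someone admitted with COVID-19 is likely to have more contact with the health service, so cases may be kept more often than non-cases. This is an inference from the rule; the documents do not report it.

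At stake are the descriptive rates of diagnosis, hospitalisation and death in healthcare workers and their breakdown by occupation. The Objectives make differences between occupational groups part of the primary aim.

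**Working it through.** **1. The plan's own figures (Sample size).** Infections: 1 400 000 × 0.062 = 86 800 (stated 86 600, 0.2% apart and not at issue here). Diagnosed: 86 600 × (1 − 0.63) = 32 042, as stated. Hospitalisations: 32 042 × 0.25 = 8010 (stated 8000). Deaths: 32 042 × 0.064 = 2051 (stated 2050). The figures reproduce.

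**2. Baseline rate and sampling error.** 8000 / 1 400 000 = 571 per 100 000. The relative 95% half-width is 1.96 / √8000 = 2.2%, or about 12.5 per 100 000.

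**3. Effect of retention that depends on outcome.** Let m be the share without ethnicity in HR and register data. Let r1 and r0 be the shares of these staff, among cases and non-cases, whose ethnicity is then found in health records. For a rare outcome,

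complete-case rate / full-cohort rate ≈ [(1 − m) + m·r1] / [(1 − m) + m·r0].

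The documents give none of m, r1 or r0, so all are assumed.

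| m | r1 = 0.9, r0 = 0.6 | r1 = 0.7, r0 = 0.6 | r1 = r0 |
|---|---|---|---|
| 5% | 0.995/0.980 = 1.015 | 0.985/0.980 = 1.005 | 1.000 |
| 15% | 0.985/0.940 = 1.048 | 0.955/0.940 = 1.016 | 1.000 |
| 30% | 0.970/0.880 = 1.102 | 0.910/0.880 = 1.034 | 1.000 |

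At m = 15% with recovery of 90% against 60%, the rate becomes 571 × 1.048 = 599 per 100 000. Three of the six cells with unequal recovery exceed the 2.2% sampling error and three do not.

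**4. The same question without assuming a mechanism.** Let m now be the share finally excluded, and RR the outcome rate in excluded relative to retained staff with the same core predictors. The ratio is 1 / (1 − m + m·RR). The full-cohort diagnosis rate is 32 042 / 1 400 000 = 2289 per 100 000. Again m and RR are assumed.

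- m = 5%, RR = 1.5: 2289 / 1.025 = 2233 (−2.4%). The shift of 56 compares with a 95% half-width of about 25 per 100 000.
- m = 20%, RR = 0.5: 2289 / 0.9 = 2543 (+11.1%).
- m = 20%, RR = 2: 2289 / 1.2 = 1907 (−16.7%).
- RR = 1: no bias at any m.

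The sign is therefore not fixed either. The health-record route pushes rates up, but other reasons for missing ethnicity could push them down.

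**5. What the named comparison can show.** Bias in a standardised rate depends on the outcome difference that remains given the core predictors. A comparison of core predictors alone does not estimate that difference.

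**The case against.** **The cohort may not be complete-case at all.** Study population defines the cohort before it mentions missing ethnicity, and words the exclusion as one from the main analysis. Outcome incidence speaks of the cohort, and the Baseline characteristics comparison requires these staff to be retained. This stands as far as it goes: the complete-case reading is inferred. The unqualified exclusions and the complete-exposure condition under Sample size make it the more natural reading. If the wider cohort was meant, the text should say so.

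**A reader might infer that the selection goes unchecked.** The documents do not support that. Missing data plans multiple imputation to test sensitivity to the exclusion and states no condition there. Missing-data patterns and the coverage of each analysis are to be reported, a flowchart will show exclusions, and a missing-ethnicity analysis is listed. Moreover, if staff lacking only ethnicity are imputed and one of these rates is re-run, the imputed value does not enter. The result is the all-staff rate, so non-random missingness does not weaken imputation for this purpose. What remains is that the better estimate would appear, at most, as a sensitivity result, while the primary rate stays complete-case without need.

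**Importance and size.** The adjusted models contain ethnicity and must have it, so only descriptive rates are affected. A selection of equal relative size in every occupation would cancel in occupational ratios, and nothing in the documents shows that it differs. Linked primary care data cover non-cases too, so a recovery gap of 30 percentage points has no documentary support. These points stand. They limit how much weight the point carries, but they give no reason to discard the staff.

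**Table detail.** An extra row or a wider comparison could be left to a fuller plan. That is fair for layout. Which staff the rates count is a matter this article addresses and leaves ambiguous.

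**Conclusion.** The point holds in a limited form. On the natural but inferred reading, the overall, country and occupation-specific rates are restricted to staff with known ethnicity, a variable they do not use. The authors themselves concede that complete-case analysis may bias and that missingness is unlikely to be random. The health-record lookup makes retention related to outcome plausible.

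Under the assumptions in step 3 the inflation is 0.5% to 10%, and zero if recovery is unrelated to outcome. The more general calculation in step 4 gives +11% to −17%. All of this rests on assumed shares, so it shows that the effect could exceed sampling error, not that it will. The documents do not show that the published rates will be materially biased, and the ethnicity-specific models are not affected. The change is worth making because it removes an avoidable selection at almost no cost.

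**What to change.** - **Outcome incidence:** define the final cohort. Compute the overall, country and occupation-specific rates in all linked healthcare workers who have the variables each rate uses (core predictors, plus occupation for the occupation rates), keeping those with missing or not-stated ethnicity.
- **Rates by ethnicity:** add an ethnicity-not-known row with events, person-time and standardised rate.
- **Baseline characteristics:** extend the recorded-versus-missing comparison to outcome rates.
- **Ethnicity models:** leave the complete-case rule and the planned imputation as they are.

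The cost is some wording, one table row and one further comparison. Denominators will differ between the rate tables and the models, which the planned flowchart can show.
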